# The effect of carotid sinus neurectomy for carotid restenosis: a study protocol for a double-blinded and randomized controlled trial

**DOI:** 10.1186/s13063-023-07871-3

**Published:** 2024-01-09

**Keywords:** Carotid endarterectomy, Carotid sinus nerve, Carotid artery restenosis, Inflammation, Randomized controlled trial

## Abstract

**Background:**

Patients undergoing carotid endarterectomy (CEA) have a high restenosis rate, which increases the risk of stroke, and there is still a lack of effective treatment for restenosis. The cause of stenosis is related to local inflammatory reactions. Some basic studies have shown that the inflammatory response causing arterial stenosis is closely related to the nerve axons distributed in its outer membrane, and that removal of the nerve is effective in reducing the inflammatory response to prevent arterial stenosis. Therefore, we propose to design a randomized controlled trial to study whether disconnecting the carotid sinus nerve during a CEA operation can reduce carotid arterial restenosis.

**Method/design:**

This study is a randomized, double-blind, single-center study. We will recruit 276 patients, who will be randomly divided into the experimental group and the control group. Based on the standard CEA operation, the operator will search for the carotid sinus nerve on the surface of the internal carotid artery and will entirely transect it in the experimental group. Both groups will be guided with the same postoperative treatment and will be followed up every 3 months for 3 years after the operation. The main indices observed will be the carotid restenosis rate, incidence and nature of carotid plaque, and carotid blood flow velocity. Other indices will be arrhythmia, blood pressure variability, and biomarkers of atherosclerosis, such as blood lipids, hypersensitive C-reactive protein (hs-CRP), homocysteine, and total bilirubin.

**Discussion:**

It is expected that carotid sinus nerve transection will significantly reduce the occurrence of restenosis after CEA, decrease the incidence of ischemic stroke, and realize the effective primary prevention of stroke.

**Trial registration:**

ChiCTR2300073652. Registered on July 18, 2023.

**Supplementary Information:**

The online version contains supplementary material available at 10.1186/s13063-023-07871-3.

## Introduction

Carotid artery stenosis (CAS) is characterized by a high prevalence and high disability rates. A meta-analysis in America showed that the overall prevalence rate of carotid artery stenosis ≥ 50% is 4.2% [1]. In China, the proportion of adults with CAS ≥ 50% by ultrasound examination is as high as 7%, and its younger trend is gradually becoming apparent, with the 40- to 64-year-old workforce accounting for 50% [2]. CAS, as an essential factor causing stroke, has attracted much attention. Studies have shown that CAS causes approximately 2530% of strokes. According to World Health Organization statistics, stroke is second only to heart disease, the leading cause of death worldwide [3].

Currently, the surgical methods for severe CAS include CEA and carotid artery stent implantation (CASI). However, patients who underwent CEA and CASI could have restenosis after the operation. It has been reported that the probability of carotid restenosis is still 5–22% even if the best drug treatment is adopted after the process [4–6]. Restenosis is usually defined as stenosis with a stenosis degree of more than 50% at a time period longer than 1 month after the operation. Compared with the first stenosis, treating patients with carotid restenosis is more challenging, and it may be dangerous to intervene in these high-risk patients again [7]. Because of the existence of scar tissue, it is usually challenging to perform CEA again because it increases the cranial nerve injury incidence. Some patients are also treated with CAS for restenosis after CEA, but the risk of recurrence after CASI treatment is more significant than that after CEA again. There is currently no clear suggestion for the treatment of restenosis. Some studies have tried to use angioplasty, carotid artery bypass, and other treatment measures [8, 9], but there is still a lack of prospective research.

It is believed that the early causes of restenosis after CEA are abnormal proliferation of the vascular endothelium and vascular remodeling. In CEA surgery, an endothelial injury occurs. Then, neointimal hyperplasia is caused by several cell-mediated chemokines, such as inflammatory cells and smooth muscle cells, which promote the pathological process characterized by narrowing blood vessels [10]. The cause of restenosis in the middle and late stages is similar to that of primary CAS, and more than 90% of restenosis is caused by carotid atherosclerosis [11].

Numerous studies have shown that the immune system participates in the formation and progression of atherosclerotic plaques by inducing leukocyte infiltration in the adventitia of arteries [12–14]. The progression of atherosclerosis is parallel to the aggregation of immune cells in the adventitia of adjacent plaques. The absence of such a collection of immune cells in the adventitia of nonplaque parts of arteries also indicates that the immune response plays a vital role in the process of atherosclerosis [15]. Andreas et al.’s research further showed that the aggregation of inflammatory cells in the plaque site is mediated by nerve axons distributed on the adventitia of this site. They found that the activity of the splenic sympathetic nerve and the abdominal vagus nerve is parallel to the progression of abdominal aorta atherosclerosis, and celiac ganglion resection can inhibit the immune response in the corresponding area of the abdominal aorta, thus inhibiting disease progression and promoting plaque stability [16].

The most easily formed part of carotid plaque is the end of CAS, which is the bifurcation of the internal carotid artery and external carotid artery. Compared with other parts, there are more nerves distributed in the adventitia of this part, and these nerves are composed of many terminal nerves from carotid sinus nerves. The carotid sinus nerve originates from the glossopharyngeal nerve, runs in front of the carotid artery approximately 1–3 cm after it exits the jugular foramen, and terminates in the carotid sinus, carotid body, and the interscalene, with a total length of approximately 4–8.8 cm and a diameter of approximately 0.5–1.5 mm [17]. The carotid sinus and carotid body are pressure receptors and chemoreceptors, respectively. Stimulating the carotid sinus has a sympathetic inhibitory effect on angiogenesis (blood pressure lowering) and the heart (bradycardia). After activation, the latter produces hyperventilation and promotes stimulation of the sympathetic nerve output of blood vessels (blood pressure increase) and parasympathetic nerve activity of the heart (bradycardia). In the treatment of carotid sinus syndrome, bilateral carotid sinus adventitia peeling has been used to inactivate carotid sinus nerves. This method has been shown to be safe and effective. Compared with the control group, there was no significant difference in blood pressure, blood pressure variability, or carotid diameter [18].

We assume that during CEA, the carotid sinus nerve on this side should be searched without enlarging the incision. It should be entirely transected to inactivate the nerves distributed in the carotid adventitia to block the inflammatory reaction mediated by the nerves at this part, prevent intimal hyperplasia and plaque formation after CEA, and control the occurrence of restenosis.

## Methods/design

### Study design

This prospective, randomized, double-blind, single-center, superiority clinical trial will be conducted at the Second Affiliated Hospital of Chongqing Medical University in China. The study was registered with the Chinese Clinical Trial Registry on 18 July 2023 (ChiCTR2300073652). The plan is to recruit 276 eligible subjects and assign them to either the control group (standard CEA therapy) or the experimental group (CEA+ carotid sinus nerve transection, CSNT) at a 1:1 ratio. Participants will be hospitalized for 2 weeks and will have a 3-year follow-up period. The trial flow chart is shown in Fig. 1.

**Fig. 1 Fig1:**
[figure not shown]
Trial flow chart

### Recruitment and eligibility criteria

Enrollment will be completed within 3 years (from the beginning of recruitment to the last patient). Enrollment is projected to begin on July 18, 2023. Recruitment advertisements for the study will be placed on the WeChat public website and hospital websites. The research staff ([name], [name], [name], [name], and [name]) will screen inpatients and outpatients according to the inclusion and exclusion criteria.

The inclusion criteria are as follows: (1) aged 55–80 years, female or male; (2) symptomatic carotid artery stenosis and noninvasive examination showed that the stenosis of the carotid artery was ≥ 70%, or angiography showed that the stenosis exceeded 50%; (3) internal carotid artery was not completely occluded; (4) National Institutes of Health Stroke Scale (NIHSS) scores ≤ 4; and (5) the patient and his or her family members were informed and provided signed and informed consent before surgical treatment. The exclusion criteria are as follows: (1) CEA or CAS surgery for unilateral or bilateral; (2) clinical status complicated by severe organ system diseases such as renal failure, heart failure, and liver cirrhosis; (3) serious psychological disease; and (4) severe arrhythmia or carotid sinus syndrome.

The withdrawal criteria are as follows: (1) voluntary withdrawal during the intervention, (2) alcohol and/or drug abuse, and (3) any other reasons considered inappropriate by the investigators.

### Outcomes

Carotid artery restenosis rate

Restenosis is defined as a degree of carotid artery stenosis ≥ 50% by ultrasound examination after CEA, and its proportion in CEA patients is the restenosis rate [1].2)Incidence and properties of carotid plaque

The proportion, size, thickness, and stability of the carotid arterial plaque3)Carotid artery blood flow velocity

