### Baseline data collection

We will request consent for review of participants’ medical records and for the collection of blood samples to assess blood lipids, hs-CRP, homocysteine, liver function, and kidney function within 1 week before the operation [20]. The blood samples after inspection will be stored in special liquid nitrogen tanks for future use in auxiliary research. On the second day after the procedure, high-resolution-enhanced magnetic resonance imaging (MRI) will be reexamined to understand the recovery of the carotid canal cavity and plaque clearance for subsequent comparison. Carotid artery color Doppler ultrasound will be performed 1 week after the operation to understand plaque.

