### Follow-up

Follow-up in the outpatient department will be performed every 3 months. At the same time, blood lipids, hs-CRP, homocysteine, liver function, and kidney function will be reexamined after obtaining informed consent. Carotid artery color Doppler ultrasound and carotid artery high-resolution enhanced MRI will be reviewed at 3 months, 6 months, 1 year, 2 years, and 2 years after the operation.

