### Comparison of baseline data

*T*-tests will be performed for quantitative data that are usually distributed, and a nonparametric test will be used for quantitative data that are not normally distributed, including blood lipids, hs-CRP, homocysteine, liver function, and kidney function. The chi-squared (*χ*^2^) test will be used for counting data, including recovery of the carotid canal cavity and plaque clearance. A two-sided *P*-value < 0.05 will be considered statistically significant.

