A consensus has been reached regarding inflammation-mediated intimal hyperplasia, vascular reconstruction, and plaque formation. However, after CEA, the best medical therapy, including inhibition of inflammation, still causes restenosis in many patients [23]. The latest research shows that although there is no nerve distribution in the intima of the blood vessel, the inflammatory reaction in this part is closely related to the nerve axons distributed on the adventitia. By removing this axon, the local inflammatory response can be eliminated, thus effectively inhibiting plaque formation and blocking the arterial stenosis caused by it [16]. Carotid stenosis mainly occurs near the bifurcation, which is just a nerve-rich area, and a small branch distribution of a single carotid sinus nerve. Simply cutting the carotid sinus nerve can achieve the effect of removing the nerve distribution.

We will use the carotid restenosis rate as the main index of the study, and at the same time, we will also select the incidence and properties of carotid plaque; carotid artery blood flow velocity arrhythmia; blood pressure variability; biomarkers for atherosclerosis, such as hs-CRP, homocysteine, and total bilirubin; and blood lipids, such as triglycerides, total cholesterol, high-density lipoprotein, low-density lipoprotein, nonesterized fatty acid, and other research indicators, to comprehensively evaluate the factors related to carotid artery blood supply and plaque formation. Follow-up began in March after the operation and will last for up to 3 years, which is consistent with most of the studies on carotid restenosis carried out at present [4–9]. Therefore, this study intends to observe the carotid restenosis rate, plaque formation, and other indicators after disconnecting the carotid sinus nerve in standard CEA surgery to confirm that this operation can effectively reduce the incidence of carotid restenosis after CEA.

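### The main endpoint sets no earliest qualifying time and does not use the planned early scans, so stenosis left by the endarterectomy can be counted as restenosis

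*Protocol article*

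**What the plan says.** All references are to the protocol article.

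- **Status of the endpoint.** The Discussion says: "We will use the carotid restenosis rate as the main index of the study".
- **Operative definition.** The Outcomes section counts stenosis of at least "50% by ultrasound examination after CEA, and its proportion in CEA patients is the restenosis rate". It names no earliest time and has no rule for stenosis that the operation left behind.
- **Reference definition.** The Introduction says: "Restenosis is usually defined as stenosis with a stenosis degree of more than 50% at a time period longer than 1 month after the operation". The two also differ on whether exactly 50% qualifies.
- **Early scans.** Under Baseline data collection, a high-resolution MRI on the second postoperative day "will be reexamined to understand the recovery of the carotid canal cavity and plaque clearance for subsequent comparison". The same section adds: "Carotid artery color Doppler ultrasound will be performed 1 week after the operation to understand plaque". Neither scan appears in Table 1.
- **Use of the early findings.** Under Comparison of baseline data, a chi-squared "test will be used for counting data, including recovery of the carotid canal cavity and plaque clearance". Nothing links these findings to the endpoint.
- **Follow-up scans.** The Follow-up section says: "Carotid artery color Doppler ultrasound and carotid artery high-resolution enhanced MRI will be reviewed at 3 months, 6 months, 1 year", with later visits after that. Table 1 also has its first follow-up ultrasound at 3 months.
- **Timing of the intervention.** Under Surgical treatment, the nerve is sought and cut only once the artery has been closed.

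**The concern.** The hypothesis in the Introduction is that cutting the nerve blocks local inflammation and so prevents new intimal hyperplasia and plaque after endarterectomy. A narrowing left by the endarterectomy is already there when the artery is closed, which is before the nerve is cut. The intervention cannot prevent it. Counting it as restenosis measures how complete the endarterectomy was, not whether nerve transection works.

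If such cases occur equally often in both arms, they add the same quantity to each restenosis rate. The absolute difference shrinks slightly, the relative reduction shrinks more, and the variance rises. The cost is power and a diluted estimate of effect. There is also a planning question: the hospital's historical rate of about 15% may or may not include residual cases, and the article does not say.

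**Working it through.** **1. Which scans can produce an event under each definition**

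| Scan | Outcomes definition | Introduction definition |
|---|---|---|
| Ultrasound at 1 week, 50% or more | can count | does not count |
| Ultrasound at 3 months, residual stenosis still above 50% | counts | counts |
| Ultrasound at 3 months or later, new stenosis above 50% | counts | counts |

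The 1-month limit alone removes only the first row. The second row needs a link to an early scan, and neither definition makes one.

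**2. Inputs**

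- Control rate 15%, one-sided testing, 0.05, 80% power, 5% dropout, 138 per arm (Sample size section).
- Evaluable per arm: 138 × 0.95 = 131.1, taken as 131.
- Analysis by chi-square on proportions (Comparison of therapeutic efficacy).
- *Assumed:* experimental rate, because none is stated.
- *Assumed:* residual rate r of 1%, 2% or 3%, equal in both arms, because none is stated.

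**3. The stated sample size**

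The figure of 276 cannot be strictly reproduced without an experimental rate. With 15% control, one-sided 0.05, 80% power and 5% dropout, several effects come close:

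- two proportions with continuity correction, 15% v 5%: 274;
- Schoenfeld log-rank, 15% v 6%: 272;
- Freedman log-rank, 15% v 5.5%: 278.

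So 276 is not shown to be wrong. I use 5% and 5.75%. At 131 per arm, an uncorrected test of 15% v 5.75% has close to 80% power.

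**4. Dilution when residual cases are added to the true rates**

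Observed rate = r + (1 − r) × true rate.

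Power = Φ{ [d√n − 1.645 √(2p̄(1 − p̄))] / √(p₁(1 − p₁) + p₂(1 − p₂)) }, where d = p₁ − p₂, p̄ is the mean of p₁ and p₂, and n = 131.

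Example, r = 3% and experimental rate 5.75%:
- p₁ = 0.03 + 0.97 × 0.15 = 0.1755; p₂ = 0.03 + 0.97 × 0.0575 = 0.0858; d = 0.0897.
- d√n = 0.0897 × 11.45 = 1.027; 1.645 × 0.4766 = 0.784; second root = 0.4724.
- Power = Φ(0.243 / 0.4724) = Φ(0.514) = 0.696.

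| r | Observed rates (5% arm) | Power | Observed rates (5.75% arm) | Relative reduction | Power |
|---|---|---|---|---|---|
| 0 | 15.0% v 5.0% | 86% | 15.0% v 5.75% | 62% | 79% |
| 1% | 15.9% v 6.0% | 83% | 15.9% v 6.7% | 58% | 76% |
| 2% | 16.7% v 6.9% | 79% | 16.7% v 7.6% | 54% | 73% |
| 3% | 17.6% v 7.9% | 76% | 17.6% v 8.6% | 51% | 70% |

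**5. If the 15% already includes residual cases**

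The true control rate is then (0.15 − r)/(1 − r), and the same relative reduction applies only to that part. At r = 3% the true control rate is 0.12/0.97 = 12.4%. The observed experimental rate becomes 0.03 + 0.12 × (0.05/0.15) = 7.0%, or 0.03 + 0.12 × (0.0575/0.15) = 7.6%. Power against 15% is 67% or 60%.

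**6. The same cases treated as non-events**

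With the true rates of step 4, the observed rates are (1 − r) times the true rates. At r = 3% these are 14.55% v 4.85% (power 85%) or 14.55% v 5.58% (power 78%). That compares with 76% and 70% when the cases are counted.

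**The case against.** The case against has real substance.

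- **The early result is checked.** A reader might infer that the plan never looks for residual stenosis. It does: the MRI is done expressly for later comparison, the 1-week ultrasound looks for plaque, and lumen recovery and plaque clearance are compared between arms. The gap is narrower: the endpoint definition does not use these findings.
- **The missing 1-month limit has little reach.** Follow-up ultrasound begins at 3 months, and the 1-week scan sits under a baseline heading. Only that one scan is affected, and only if it is read as an outcome scan. The Outcomes wording permits that reading but does not require it.
- **The Introduction has no exclusion for residual stenosis either.** On persistence to 3 months the two definitions agree, so this part is a proposed improvement, not a contradiction.
- **Adjudication detail is often left to the full protocol or analysis plan.** That is true in general. Here, however, the article states a complete operative definition, and it is looser than the reference definition it cites.
- **Counting all postoperative stenosis is a defensible ITT choice.** Both early scans follow the randomised procedure, and equal residual rates in the two arms are assumed, not shown. This stands as a caution on the remedy and is why a sensitivity analysis is needed.

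Two stronger readings are not supported. One is that technical failures are in fact being counted: that is a possible consequence of the wording, and the article gives no residual rate. The other is that disease in the unoperated artery counts. The artery is not named, but restenosis after endarterectomy naturally means the treated vessel, so that reading is strained.

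**Conclusion.** The point holds in a limited form. The main endpoint omits the time limit that the article itself cites and makes no use of early scans that are already planned. Applied literally, stenosis that nerve transection could not have prevented may enter the restenosis rate.

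The consequence is loss of power and a diluted effect; if residual rates are equal, neither arm is favoured. The size cannot be established from the article. Under the stated assumptions (15% control, 5% to 5.75% experimental, 131 per arm, one-sided 0.05), a residual rate of 1% costs about 3 percentage points of power and a rate of 3% costs about 9 to 10. The loss is larger if the 15% planning rate already contains residual cases. This is a worthwhile tightening of the definition. It does not show that the trial is biased or the sample size wrong.

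**What to change.** 1. In the Outcomes section, define the main event as stenosis of 50% or more of the operated carotid artery, on a scheduled ultrasound more than 1 month after surgery, that was not already present on the 1-week ultrasound. Bring the Introduction and Outcomes wording into line on whether exactly 50% qualifies.
2. Report residual stenosis at 1 week separately by arm.
3. Keep every randomised patient in the ITT set. State that patients with residual stenosis are non-events in the primary analysis, and add a sensitivity analysis that counts them as events.
4. Add the day-2 MRI and the 1-week ultrasound to Table 1.
5. Confirm that the 15% planning rate was obtained under the same definition; if not, restate it.

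The cost is wording, one table edit and one sensitivity analysis. No new scan is needed, and the Trial status section reports only 13 patients recruited. There are two downsides. Slightly fewer events are counted: with 3% residual stenosis, power is about 1 percentage point below the case with none. And the 1-week scan is a post-randomisation measurement, so patients classed as residual cannot have a primary event; the sensitivity analysis shows whether that matters.

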### Sample size

The determination of sample size was calculated by SPSS 23.0 software. Based on a previous study and clinical assumptions, carotid restenosis was 5–22% [4–6]. Our previous research showed that the restenosis rate of the carotid artery after CEA in our hospital was approximately 15%. The statistical parameters were set as follows: one-sided log-rank testing with 80% power, the probability of obtaining a false-positive with a statistical test at 0.05, and a 3-year follow-up time. Considering a potential dropout rate of 5% across both groups, it is estimated that 276 patients will need to be enrolled (138 participants per group).

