### Data collection and management

A case report form (CRF) will be completed by each participant before the intervention. The collection of baseline data, along with primary and secondary outcomes, will be recorded entirely in the CRF. Each participant (corresponding to a CRF) will be assigned a specific number by which the intervention and follow-up will be performed. Using ResMan, an Internet-based electronic data capture (EDC) tool, all information will be kept independently as double copies in a computer. The data files will be locked after a blind audit and when they are confirmed reliable. The CRF shall be owned by the principal investigator and shall not be provided to any third party in any form without the written approval of the principal investigator, who will oversee all of the final trial data. A follow-up registration form will be given to all patients to encourage retention. A researcher will collect the reason for the loss, survival condition, and recent outcome as an assessment for participants who stop the intervention. The original paper files will be kept in the filing cabinet of the sponsoring organization, and clinical data will be held for 5 years.

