### Statistical analysis

We will use SPSS 23.0 statistical software for Windows to perform statistical analysis. To ensure the reliability of our conclusions, we plan to use intention-to-treat (ITT) analysis as the primary form of research.

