### Comparison of therapeutic efficacy

The rate of carotid artery restenosis, plaque incidence, and stability of carotid arterial plaque will be analyzed by the chi-square (*χ*^2^) test between the two arms.

The size and thickness of carotid arterial plaque, carotid artery blood flow velocity, blood lipids, hs-CRP, homocysteine, and total bilirubin will be analyzed by *t*-test analysis.

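### The main endpoint is compared as a simple proportion by chi-square although the trial was sized on a log-rank test, so unequal death or loss between arms can bias it

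*Protocol article*

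**What the plan says.** All references are to the protocol article.

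- **Outcomes.** Restenosis is ultrasound stenosis of at least 50% after CEA, and "its proportion in CEA patients is the restenosis rate". No time point or scan requirement is attached to that proportion.
- **Discussion.** This is the main endpoint: "We will use the carotid restenosis rate as the main index of the study".
- **Statistical analysis.** "we plan to use intention-to-treat (ITT) analysis as the primary form of research".
- **Comparison of therapeutic efficacy.** "The rate of carotid artery restenosis, plaque incidence, and stability of carotid arterial plaque will be analyzed by the chi-square" test.
- **Sample size.** The design rests on "one-sided log-rank testing with 80% power", with "the probability of obtaining a false-positive with a statistical test at 0.05", 3 years of follow-up and a control restenosis rate of about 15%. Enrolment is inflated for loss ("Considering a potential dropout rate of 5% across both groups") to 276 patients, 138 per group.
- **Data collection and management.** For participants who stop, "A researcher will collect the reason for the loss, survival condition, and recent outcome". The section does not say how this information enters the restenosis rate.
- **Table 1.** Ultrasound is scheduled at 3 and 6 months and at 1, 2 and 3 years.

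**The concern.** The design and the analysis treat the same patients differently. Under the log-rank test used for sizing, a patient who is lost leaves the risk set and contributes the time actually observed. Under the chi-square test named for the analysis there is no risk set, only a yes cell and a no cell. Someone who dies or stops attending before a positive scan must go in the no cell or be left out.

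Patients are aged 55 to 80 with symptomatic disease, have surgery and are followed for 3 years, so some deaths and losses should be expected. If they are more frequent after transection and are scored as no restenosis, the main endpoint moves in favour of transection. The Interim analysis section also ends the trial if the restenosis rate is significantly higher in the experimental group, so the same bias would push that rule away from stopping. The comparison in the Safety evaluation section names arrhythmia and blood pressure variability but not death, so it would not act as a counterweight.

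**Working it through.** **The plan's own figure.** The total of 276 cannot be reproduced from stated inputs, because no restenosis rate or hazard ratio is given for the transection arm. Back-solving at one-sided 0.05, 80% power and 5% loss gives totals close to 276:

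- 15% vs 5%, two proportions with continuity correction: 274
- 15% vs 5.5%, Freedman log-rank: 278
- 15% vs 6%, Schoenfeld log-rank: 272

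The point made here does not depend on which of these was used.

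**Inputs for the bias check.**
- From the article: 138 per arm, 15% restenosis, 5% loss overall, one-sided 0.05.
- Assumed: no true effect (15% in both arms), the split of loss between arms, and patients dead or lost before a positive scan scored as free of restenosis.

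**Formula.** Observed rate = true rate × (1 − share dead or lost before a positive scan). The false-positive rate is the normal-approximation probability that the pooled two-proportion test favours transection.

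| Loss, control / transection | Overall loss | Observed control | Observed transection | False gap (points) | One-sided false-positive rate |
|---|---|---|---|---|---|
| 5% / 5% | 5% | 14.25% | 14.25% | 0 | 5.0% |
| 5% / 10% | 7.5% | 14.25% | 13.50% | 0.75 | 7.2% |
| 0% / 10% | 5% | 15.00% | 13.50% | 1.50 | 9.9% |
| 5% / 15% | 10% | 14.25% | 12.75% | 1.50 | 10.0% |

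**Worked row, 0% / 10%.** This is the extreme split of the planned loss: 5% of 276 is 13.8 patients, which is 10% of one arm of 138. Control: 0.15 × 1.00 = 0.150. Transection: 0.15 × 0.90 = 0.135. Gap: 0.015, or 0.015 × 138 ≈ 2 patients. The null standard error is √(2 × 0.1425 × 0.8575 / 138) ≈ 0.0421, and the standard error under the two observed rates is also about 0.0421. The test favours transection with probability Φ((0.015 − 1.645 × 0.0421) / 0.0421) ≈ 0.099.

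**Two-sided test.** At two-sided 0.05, the chance of a significant result favouring transection rises from 2.5% to 3.8% for 5% / 10% and to 5.4% for 0% / 10%.

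**Earlier detection.** If half of these patients' restenoses had been found before they left, the gaps halve. For 5% / 10% the gap is about 0.38 points (one-sided 6.0%), and for 0% / 10% it is 0.75 points (7.1%).

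**The case against.** The strongest objection is that the article never says in words that an unscanned patient counts as negative. The denominator is CEA patients, not explicitly all of them. Intention to treat is named without a missing-data rule, and a condensed article may leave such a rule to an analysis plan that is not shown. Survival status and reasons for loss are collected, so that plan would have material to work with. This stands, and it limits the wording: scoring as free is an inference from the Outcomes and Statistical analysis sections. It does not remove the point. The complete-case alternative departs from the stated intention-to-treat principle, and on either reading the test named for the analysis is not the one the trial was sized on. That mismatch is stated in the article and is more than a missing detail.

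Three stronger readings are tempting but not supported:

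- **The 5% allowance sets up a second, incompatible denominator.** It does not. Inflating enrolment for dropout is a routine power allowance and is compatible with analysing everyone randomised.
- **A large part of the hoped-for benefit could be spurious.** That needs loss well above plan (5% versus 20% is 12.5% overall), no restenosis detected before loss, and a design effect that the article never states. No mortality or loss by arm is given.
- **A competing-risks estimate would cure the problem entirely.** It would not. Cumulative incidence with death as a competing event still keeps patients who died in the denominator as never restenosed. Without censoring it equals the crude proportion. It deals with loss, not with excess deaths.

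**Conclusion.** The concern holds in a limited form. The article fixes an analysis that cannot censor for a trial designed on one that can, and this leaves the main comparison open to bias when death or loss differs between arms. With no true effect and the natural scoring, the false gap is at most about 1.5 points at the planned 5% overall loss, and only if all of that loss fell in the transection arm. It is 0.75 points for an assumed 5% versus 10%. The corresponding one-sided false-positive rates are about 9.9% and 7.2% against a nominal 5%. Equal loss creates no gap under the null and only lowers both rates.

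These sizes rest on the assumed splits by arm and on no restenosis being detected before loss. With five scheduled ultrasound visits, some restenosis will be detected first, so they are upper figures for each split. The article should not be read as declaring death or loss a success. It leaves that as the natural consequence of its endpoint and test.

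**What to change.** In Comparison of therapeutic efficacy, make the primary comparison a time-to-event analysis of all randomised patients, to match the Sample size section: a log-rank test on time to first ultrasound stenosis of at least 50%, with patients lost censored at their last scan. Keep the set as all randomised patients; limiting it to those who undergo CEA would depart from intention to treat.

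Beside it, report the 3-year cumulative incidence by arm with death as a competing event. Because that estimate still counts deaths as never restenosed, also report deaths by arm and prespecify a restenosis-or-death analysis as a sensitivity analysis.

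If the chi-square is kept, impute missing 3-year status from the earlier scans and state that missing status is not scored as no restenosis.

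The cost is revised wording and a little more analysis work. The repeated scans and the collection of survival status are already planned, so no new data are needed. Censoring still assumes that loss is unrelated to restenosis risk, so the reasons for loss should be tabulated by arm.
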